**JUSTIFICATION**

HIV and cervical cancer are diseases that disproportionately affect women in resource-limited settings. The challenge of reducing cervical cancer in developing countries is too complex to be overcome simply by introducing current detection methods from resource-rich countries into resource-limited areas. The infrastructure—facilities, equipment, and personnel—and training required for conducting a proper examination, collecting a high-quality sample, transporting the sample to a well-trained lab and adequately performing the tests present significant barriers that hamper effective implementation of known screening technologies in low-resource settings. Novel strategies that have received attention recently include VIA and biomarker testing, for the benefits outlined above. VIA has been widely studied and even implemented in resource-limited settings, but has not yet been validated among HIV-infected women. Testing for p16^INK4a^ has never been carried out among HIV-infected women in resource-limited settings, where it could have the most impact. We will define the test characteristics and identify a cut-off value for “positive” in this population, using a biochemical assay which has the potential to be developed into a point of care test. In addition, we will compare p16^INK4a^ test performance with HR-HPV which is the most commonly known biomarker available. The high prevalence of HR-HPV among HIV-infected women in Kenya makes us believe that this test would have low specificity for CIN2/3.^79^ It is important to compare the two currently available biochemical tests side-by-side, to inform clinical decisions and development of screening strategies in this population.

HIV-infected women are at increased risk for HR-HPV-related cervical dysplasia and cervical cancer, yet the impact of HR-HPV and cervical dysplasia on HIV-infectivity is relatively unknown. The evidence for increased HIV-1 genital shedding in the presence of other sexually transmitted infections or inflammation, along with the preliminary data on HR-HPV and CIN in HIV-infected women suggest that these may also increase HIV-1 genital shedding. This study improves on the preliminary work mentioned above in several ways. We will exclude women with concomitant cervical or vaginal infections, which may have independent effects that cannot be controlled for in the analysis. Our study population will include women on HAART, reflecting the increased numbers of women now on treatment. Finally, we will use CIN rather than HR-HPV as a predictor. CIN is well-accepted to be the result of persistent HR-HPV infection and clinical decision-making regarding treatment is based on the diagnosis of CIN, not HR-HPV.^80, 81^ The high HIV and HR-HPV co-infection rate in Kenya and the high proportion of HIV-serodiscordant partnerships in Kisumu make this study both feasible and important for this population. The FACES/UCSF relationship and the existing well-accepted cervical cancer screening program both combine to facilitate study-related activities. We also seek to provide researchers and clinicians with information about the potential increase in HIV-infectivity related to diagnosis of and treatment for cervical dysplasia, which could have an immediate impact on recommendations for length of post-procedure abstinence among women whose partner’s HIV status is negative or unknown. It will also be useful in the design of future studies to compare the efficacy and safety of different diagnostic and treatment modalities for cervical dysplasia among HIV-infected women. Finally, data about magnitude and duration of increased HIV shedding can be added to decision analysis models to estimate the impact, cost-benefit and cost-effectiveness of various treatment methods.

**HYPOTHESES (NULL)**

1. VIA, VILI and p16^INK4a^ will perform equally well as screening tests for cervical cancer in HIV-infected women.
2. Women with CIN2/3 will have the same frequency and quantity of HIV-1 RNA detected in their genital secretions as women without CIN2/3.
3. Women treated with LEEP will have the same quantity of cervicovaginal HIV-1 RNA detected pre- and post-treatment and up to 14 weeks after the procedure.

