**OBJECTIVES:**

General:

We seek to establish the link between the presence, diagnosis and treatment of cervical dysplasia and HIV genital shedding. We also seek to establish the sensitivity and specificity of three resource-appropriate screening methods, VIA, VILI and p16^INK4a^ biomarker testing, for cervical dysplasia.

Specific (Aims):

**Aim 1:** **To calculate the sensitivity, specificity, and the positive and negative predictive values of visual inspection of the cervix after application of 3-5% acetic acid (VIA) and visual inspection with Lugol’s Iodine (VILI) for the diagnosis of cervical intraepithelial neoplasia grade 2 and grade 3 (CIN2/3) in HIV-infected women.** HIV-infected women enrolled in care at the FACES clinics in western Kenya will undergo VIA or VILI and colposcopy with directed biopsy as indicated. The colposcopy will be used as the reference standard, allowing for calculation of sensitivity, specificity, positive and negative predictive value of VIA and VILI.

Hypothesis 1: VIA and VILI will have test characteristics validating their use as a screening test for cervical dysplasia among HIV-infected women in resource-limited settings.

**Aim 2: To define the quantitative value of a biochemical assay for p16^INK4a^ that predicts cervical neoplasia with the greatest sensitivity and specificity among HIV-infected women using a receiving operating characteristic (ROC) curve.**

**Aim 2a: To compare the sensitivity and specificity of the p16^INK4a^ biochemical assay with that of HR-HPV testing.** HIV-infected women enrolled in care at the FACES clinics in western Kenya will undergo specimen testing for p16^INK4a^ and HR-HPV, followed by colposcopy with directed biopsy as indicated.

**Aim 2b: To calculate the sensitivity and specificity of the p16^INK4a^ biochemical assay for the detection of CIN2/3 using colposcopy as the gold standard.** HIV-infected women will have p16^INK4a^ specimens collected prior to colposcopy. Diagnosis for positive p16 will be based on the ROC curve cut-off determined in the pilot study, with colposcopy as the reference standard as above.

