We propose a ***cross-sectional*** study to evaluate this specific aim. Each participant will undergo a VIA or VILI with specimen collection for p16^INK4a^ and HR-HPV and colposcopy by a different clinician during a single clinic visit. The study clinician performing the colposcopy will be blinded to the results of the VIA or VILI. For women in the VILI arm, the colposcopy will be performed first in order to eliminate any interference with colposcopy interpretation from the iodine staining. Biopsy decisions will be made at the time of colposcopy, but deferred until after the VILI. Any woman with cervical lesions suspicious for dysplasia seen at the time of colposcopy will undergo biopsy. Colposcopy will be used as the reference standard for presence or absence of CIN2/3, with biopsy results being the final diagnosis when available. Women with a normal colposcopy without biopsy will be considered to have no disease.Specific Aims 1, 2, 2a and 2b)

We propose a **prospective cohort** study using a subset of women identified from the cross-sectional study in Specific Aims 1 and 2a to evaluate specific aim 2c during a one-year follow-up visit. We will recruit women for this follow-up study who participated in the pilot p16^INK4a^ ELISA study (Aim 2a) and had normal colposcopy or CIN1. In a single visit, each participant will undergo a VIA with specimen collection for p16^INK4a^ and HR-HPV followed by colposcopy and biopsy if needed.

We propose a ***case-control*** study to measure and compare the presence and quantity of HIV-1 RNA in the cervicovaginal specimens of women with biopsy-confirmed CIN2/3 (cases) and age-matched women without evidence of cervical disease as measured by negative VIA (controls). We will compute the odds ratio for HIV-1 detection and compare log transformed mean viral loads between cases and controls. (Specific Aim 3)

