The main outcome for this specific aim will be p16^INK4a^ values. Monoclonal antibody testing for p16^INK4a^ will be performed on all specimens using an ELISA-based biochemical assay currently available only in specified research laboratories. Samples for the p16^INK4a^ ELISA will be transferred into a collection vial with a prototypic sample lysis medium (MTM Laboratories, Heidelberg, Germany) containing nonionic detergents (<1%). Lysed samples will be stored frozen until the ELISA-based measurement of p16^INK4a^ protein concentration is performed. Next, 100-µL aliquots of each individual sample were subjected in duplicate to a prototypic colorimetric sandwich-ELISA protocol (MTM Laboratories), which is based on two different p16^INK4a^-specific monoclonal antibodies, an antibody that was coated to the solid phase of a microtiter plate (clone E6H4) and an antibody that was conjugated to horseradish peroxidase for the detection of captured p16^INK4a^ protein (clone D7D7). For quantification, calibration curves will be established by using reagent standards that contained known concentrations of p16^INK4a^ antigen. p16^INK4a^ protein concentrations in the clinical samples were calculated as arbitrary units (U/mL) based on the standard curve. Average values of double measurements were used, and the coefficient of variation was <15% at a cutoff value of 16 U/mL. In order to ensure the reliability of the biochemical assay measurements, quantitative levels of p16^INK4a^ will be compared with levels found in immunohistochemical (IHC) staining of the corresponding biopsy specimens. Correlation will be determined through the calculation of a Kappa coefficient, which we seek to be greater than 0.8. In cases of normal colposcopy (and hence no biopsy), p16^INK4a^ IHC values will be assigned as zero. The IHC staining will be done by pathologists at KEMRI, who have experience in this technique and will undergo further study-specific training coordinated by [name] [name] at the German Cancer Research Center in Heidelberg.

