Data Storage: The study will be conducted within the existing clinic settings in the Nyanza Province. Data will be collected from the electronic medical record and on study-specific forms (Appendices F and G). Study data will be included as part of the patient’s medical file and maintained in locked file cabinets within the clinic. Data will be abstracted to computers by data entry clerks and managed by the assigned data manager at each site. Abstracted data will be labeled by unique study ID only. A file correlating study ID and medical file number will be kept in separate password-protected Excel computer file and accessible only to the core research team. Additionally, all study computers are password protected and kept in locked offices within the clinics.

Statistical Analysis:

Statistical analysis for all specific aims will be carried out using STATA and SPSS software.

**Specific Aim 1**: The goal of specific aim 1 is to calculate the sensitivity, specificity and predictive values of VIA and VILI for CIN2/3, with colposcopy as the gold standard. Colposcopy will be performed on every participant, regardless of screening result, to avoid verification bias.^92^ To calculate the sample size for this study, we assume that the prevalence of CIN2/3 among HIV-infected women at FACES will be 7%, as has been seen in the cervical cancer screening program at FACES.^78^ Sample size calculations will be based on prior estimates of VIA sensitivity, as these are more prevalent and therefore have more precision.

Sensitivity: Previous studies have shown that VIA has a sensitivity of 60-86%^39, 40, 91, 93-97^ for detection of CIN2/3 among healthy women, which is comparable to the sensitivity of cervical cytology and would be an acceptable test characteristic for this setting. In order to determine sensitivity, we will construct a 2 x 2 table, and divide the number of women with a true positive VIA result (i.e. those with disease diagnosed by colposcopy and VIA) by the number of true positive VIAs plus the number of false negative VIAs. Specificity: Specificity values for VIA range from 64 to 94% for the detection of CIN2/3.^39, 40, 91, 98, 99^ To determine specificity of VIA, we will divide the number of participants with true negative VIA (i.e. has no disease diagnosed colposcopically) by the number of true negative tests plus the number of false positive tests.

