In addition to sensitivity and specificity, we will calculate the positive and negative predictive values of VIA. Studies have shown a PPV of VIA for CIN2/3 to range from 9-27% in HIV-negative women.^97, 100, 101^ To calculate the PPV in our study, we will divide the number of participants with a positive VIA by the number of participants found to have CIN2/3 on biopsy. VIA has been shown to have a negative predictive value (NPV) of 91-99.5% in HIV-negative women.^102^ To calculate the NPV, we will divide the number of participants with a negative VIA by the number of participants with no evidence of disease at colposcopy, either by visual impression or a negative biopsy result. Confidence limits for estimates of sensitivity, specificity, PPV and NPV will be exact, based on the binomial distribution.

Finally, we will compare the test characteristics between the two screening modalities using a McNemar’s test of proportions.

**Specific Aim 2**: To determine the cut-off value for the p16^INK4a^ biochemical assay that will provide the highest sensitivity and specificity for the detection of CIN2/3, we will construct a Receiver Operating Characteristic (ROC) curves using the results of the ELISA-based assay and the histology specimens. An ROC curve will allow us to plot the True Positive Rate (TPR) and the False Positive Rate (FPR) for various values of the p16^INK4a^ assay. As TPR is equivalent to the sensitivity of a test, and 1-FPR is the specificity, the graphical representation, as well as the calculated Area Under the Curve will allow us to determine the cut-off value for p16^INK4a^ to define a “positive test” with the highest sensitivity and specificity.

We will compare the absolute differences in sensitivity and specificity for detection of CIN2/3 of p16^INK4a^ and HR-HPV using the Mann-Whitney U test. The values of p16^INK4a^ will be determined from the ROC curves in Specific Aim 2. The sensitivity and specificity of the HR-HPV tests will be calculated as below:

- To calculate **sensitivity**, we will divide the number of women with a true positive test by the number of true positives plus the number of false negative HR-HPV testing.
- To calculate **specificity**, we will divide the number of participants with no disease diagnosed colposcopically (true negatives) by the number of true negative plus false positive HR-HPV tests.

Confidence limits for estimates of sensitivity and specificity will be exact, based on the binomial distribution.

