**EXPECTED APPLICATION OF RESULTS**

Specific Aims 1 and 2 will define the test characteristics for VIA and VILI as well as the parameters for a p16^INK4a^ biochemical assay for use in this population, which would be its first trial among HIV-infected women. This will provide not only a direct comparison, but will help validate the use of either or both low-cost tests in the setting of an HIV-care clinic. An ELISA-based biochemical assay can be developed into a simple test that can could be run immediately without water or electricity requirements, similar to a urine pregnancy, blood glucose or HIV-test. Development of a point-of-care test for a biomarker with high sensitivity and specificity for CIN will exponentially increase access to cervical cancer screening in resource-limited settings.

Specific Aims 3 and 4 will provide preliminary data for a larger trial looking at HR-HPV and HR-HPV-related high-grade CIN as risk factors for HIV-transmission. Aim 4 will provide preliminary data about the levels and time-course of post-treatment HIV-1 genital shedding, providing a better understanding of potential risks of cervical dysplasia treatment among HIV-infected women. These findings will guide pre- and post-procedure counseling to ensure women’s safety and minimize risk of HIV transmission as well as aid in the design of a randomized trial that incorporates HIV genital shedding as a safety outcome to be compared by treatment arms.

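### Null hypothesis 1 sets p16 against VIA and VILI, but the analysis section names no test of p16 against either visual test

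*Protocol*

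**What the plan says.** **The commitment.** Item 1 of *Hypotheses (Null)* states that VIA, VILI and p16 "will perform equally well as screening tests for cervical cancer in HIV-infected women". The general objective covers the same three tests, as estimation only: "We also seek to establish the sensitivity and specificity of three resource-appropriate screening methods, VIA, VILI and p16". *Expected Application of Results* first names VIA, VILI and the p16 assay, then continues: "This will provide not only a direct comparison, but will help validate the use of either or both low-cost tests".

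**The data.** *Study Design*: "Each participant will undergo a VIA or VILI with specimen collection for p16" and HR-HPV, with colposcopy at the same visit. Under *Quality Assurance*, p16 antibody testing "will be performed on all specimens using an ELISA-based biochemical assay". The sample size text gives 900 women to VIA and 900 to VILI, and Aim 2b (p16 accuracy) takes over the Aim 1 sample. *Objectives* has Aim 2b use the cut-off from the pilot ROC curve.

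**The analyses.** The Aim 1 text opens with "The goal of specific aim 1 is to calculate the sensitivity, specificity and predictive values of VIA and VILI for CIN2/3" and closes with "Finally, we will compare the test characteristics between the two screening modalities using a McNemar" test of proportions, without naming the two modalities. The Aim 2 text compares the sensitivity and specificity of p16 with those of HR-HPV. Aim 2b sets p16 against colposcopy alone.

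**The concern.** A hypothesis that puts three tests in one equality statement needs an analysis that sets each against the others. Here p16 is formally compared only with HR-HPV, which is not in that hypothesis. Followed as written, the protocol would give separate accuracy estimates for p16 and for each visual test but no inference on the difference between them. Readers would be left to compare two intervals by eye, which ignores that both results come from the same woman.

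The one paired test named sits in the Aim 1 section, where it most naturally refers to VIA and VILI. Those two are done in different women, so there are no pairs for McNemar's test to use. The contrast that is paired has no test assigned to it.

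**Working it through.** **1. Hypothesis against planned comparisons**

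| Contrast | In null hypothesis 1? | Same women? | Named analysis |
|---|---|---|---|
| VIA vs VILI | yes | no (900 and 900) | McNemar, on the natural reading |
| p16 vs VIA | yes | yes, VIA arm | none clearly named |
| p16 vs VILI | yes | yes, VILI arm | none clearly named |
| p16 vs HR-HPV | no | yes | Aim 2 comparison |

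The protocol gives no sample size or power for p16 versus a visual test, so there is no stated figure to reproduce.

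**2. What the planned sample could support**

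Inputs from the protocol: 900 women per arm, CIN2/3 prevalence 7%, VIA sensitivity 75% and specificity 80%, two-sided alpha 0.05. Assumed here: 80% power, and a discordant proportion ψ of 20% or 30%.

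- Cases per arm: 900 × 0.07 = 63. Non-cases per arm: 900 − 63 = 837.
- McNemar sample size for a paired difference δ: n = (1.96√ψ + 0.842√(ψ − δ²))² / δ².
- Sensitivity, n = 63: δ ≈ 15.5 points at ψ = 20% and 19.0 points at ψ = 30%. Check of the second: (1.074 + 0.432)² / 0.19² ≈ 63.
- Specificity, n = 837: δ ≈ 4.3 and 5.3 points.

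**3. Are these sensitivity differences possible?**

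If p16 is the better test, the share of cases that are p16-positive and VIA-negative is (ψ + δ)/2. It cannot exceed 1 − 0.75 = 25%.

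- ψ = 20%: (20 + 15.5)/2 ≈ 18%, possible.
- ψ = 30%: (30 + 19)/2 = 24.5%, only just possible.
- ψ = 40%: δ ≈ 22 points and (40 + 22)/2 = 31%, impossible. That value is not used.

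A second route assumes p16 sensitivity and a within-woman correlation of 0 to 0.3. Against VIA at 75% with 63 cases, power is 28-38% for p16 at 85%, 59-73% at 90% and 88-94% at 95%.

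**4. Effect of reusing the women who set the cut-off**

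The pilot plan has 140 positive colposcopies with a 57% predictive value for CIN2/3: 140 × 0.57 ≈ 80 cases. The full sample is expected to hold 1,800 × 0.07 = 126. If the pilot women are among the 1,800 and are excluded, 126 − 80 = 46 cases remain, or 23 per arm with an equal split (assumed).

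At n = 23 and ψ = 30%, even δ = 30 points, with every discordant pair in one direction, gives power Φ((0.30√23 − 1.96√0.30)/√(0.30 − 0.09)) = Φ(0.80) ≈ 79%. So the detectable difference is about 30 points. That is more than the 25-point gain available to p16 over a 75% VIA. At that ceiling (ψ = δ = 25%) power is Φ((0.25√23 − 1.96√0.25)/√(0.25 − 0.0625)) = Φ(0.51) ≈ 69%.

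**The case against.** **The McNemar sentence may already be the missing comparison.** The abstract names VIA and protein biomarkers as the two methods under test and brings in VILI for a small subset. McNemar's test also fits p16 versus a visual test and does not fit VIA versus VILI. This reading is possible, so it would be too strong to say that the protocol certainly plans no such comparison. It is still the weaker reading: the sentence closes a section whose stated goal is VIA and VILI. If it were right, VIA versus VILI would have no test instead. The sentence needs clarifying either way.

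**The aims do not promise it.** The hypotheses under *Objectives* are that VIA and VILI have acceptable characteristics and that p16 exceeds HR-HPV. The planned analyses serve those. This stands, and it limits the point. A reader might infer that the study fails its main question, visual test or biomarker. The protocol does not rank that question first, and *Justification* singles out p16 versus HR-HPV as the important side-by-side comparison. The mismatch is with null hypothesis 1 and with the expected-results text, which itself does not name the pair to be compared.

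**A separate analysis plan may add the contrast.** It may. But the protocol does not defer the matter: it lists its hypotheses and its comparative tests, and the two lists differ.

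**The test is not free of difficulty.** A reader might infer that the paired test can simply be run on everyone. *Study Design* puts Aims 1, 2, 2a and 2b in one cross-sectional study, so women who set the p16 cut-off may be in the comparison sample, which would favour p16. The overlap is not certain, but it has to be dealt with.

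**Conclusion.** The point holds as a mismatch between a stated hypothesis and the named analyses. The p16 part of null hypothesis 1 has no clearly assigned test, and the one paired test named is attached, on its natural reading, to an unpaired contrast. The separate accuracy estimates are unaffected.

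The size depends on whether pilot women are reused. Before any exclusion, each arm can detect about 16 to 19 points in sensitivity and 4 to 5 points in specificity, given 7% prevalence, 80% power and 20-30% discordance (assumed). After removal of about 80 pilot cases, split equally between arms, the sensitivity figure is about 30 points. That comparison should therefore be labelled secondary or exploratory. The figure of 80 comes from the pilot plan: the Aim 2c text reports 55 CIN1 and 190 normal women from the pilot but no count of CIN2/3.

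**What to change.** 1. In the Aim 1 analysis text, name the two tests that the McNemar sentence compares. If they are VIA and VILI, replace McNemar's test with a comparison of independent proportions.
2. Add paired McNemar comparisons, with intervals for the paired difference, of p16 at the pilot cut-off against VIA in the VIA arm and against VILI in the VILI arm. Do this separately in women with CIN2/3 (sensitivity) and without it (specificity).
3. State whether the pilot women are among the 1,800. Exclude those whose data set the cut-off, or correct for optimism.
4. Label the sensitivity comparison secondary or exploratory, and report its interval.

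If the investigators do not want this comparison, remove p16 from null hypothesis 1 and reword the direct-comparison sentence in *Expected Application of Results*.

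The first route costs some analysis on results already planned, with no new specimens or visits. The price of excluding pilot women is lost precision for sensitivity. The second route is a change of wording.
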